Stage 1 “Creating the Clinical Foundation”: This stage will allow participants to learn and practice shared decision-making by cocreating treatment goals, identifying thought patterns, and identifying coping skills and defense mechanisms. The goal of this stage is for participants to develop a broad understanding of their thoughts and behaviors while beginning to identify strengths and need areas. Participants will also be introduced to clinical language and definitions for shared language to be established.Stage 2 “Building Clinical Skills”: Expanding from the skills learned in stage one, this stage will focus on teaching and practicing cognitive defusion and behavioral activation techniques. The goal for this stage is to expose participants to practical therapeutic skills that can be used across many situations and symptom management.Stage 3 “Solidifying Clinical Gains”: This stage introduces participants to mindfulness techniques, a diary card–like model, and patient activation and empowerment skills. The purpose of this stage is to ensure participants grasp all technical skills and clinical language reviewed throughout treatment to make informed autonomous decisions regarding treatment preferences.

This yearlong study will follow a prospective longitudinal cohort design where all participants will receive the same treatment and smartphone interventions. Based on our own Digital Clinic pilot data, we hypothesize participants will report a treatment response rate—defined as 50% symptom reduction—of improvements in anxiety and depression within the 8 weeks of treatment compared to their initial baseline. We also hypothesize that both rates of app engagement out of sessions, as well as therapeutic alliance measured during sessions, will be correlated with clinical improvements and suggest a mechanism of action for TECC. Furthermore the study will test the feasibility of providing technology-enabled mental health care within an outpatient clinical setting via virtual telehealth visits, explore the linguistic and cultural appropriateness of the smartphone app (mindLAMP) used in the study, and analyze the symptom changes of anxiety and depression for all study participants.

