### Interventions

Interventions for TECC will be employed through a multipronged approach including in-session care from clinicians, exposure and education to evidence-based therapies, use of the mindLAMP app, and technology support from the digital navigator.

At least 1 week before the initial clinical visit, participants will meet with the digital navigator to download the mindLAMP app, receive app training, and will be asked to begin completing the mood surveys (PHQ-9 and GAD-7) in mindLAMP on a daily basis. During the meeting, participants will be informed the app will not be used to offer emergency services between sessions and app responses will not be monitored outside of clinical sessions. A signed waiver will be presented to reflect this understanding.

The format for TECC sessions will follow the pre-established Digital Clinic structure (Figure 1). Specifically, before each clinical session, participants will be required to complete a variety of clinical surveys. These surveys will be made available through the clinic’s secured, research-based survey platform (REDCap, Vanderbilt University). The surveys (see Figure 2 for more details) are designed to help clinicians develop a comprehensive understanding of each participants progress throughout the study. Once the clinical portion of the session starts, any mindLAMP data collected will be reviewed and discussed. This step will ensure the data in mindLAMP accurately reflects the participant’s lived experience and ensure the personalized nature of each patient’s care is reflected in the session. Next, the clinician will discuss a predetermined clinical skill, and the clinician will work to relate the skill to the patient’s unique needs. The clinician will introduce the skill by describing its purpose, giving examples of when the skill can be used, and explain how the skill could impact the participants mental health needs. With clinician guidance, participants will then practice the skill, brainstorm scenarios in which the skill could be used, and review a skill-building activity (see Multimedia Appendix 1 for details). Activities will be conducted through skill-building modules (eg, mindfulness), informational worksheets, surveys, and free-writing opportunities that will be available through the app. Participants will be encouraged to complete the activities between sessions to strengthen their understanding and comfortability of use with each skill.

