### Study Measures

Since TECC was designed to collect a number of clinical surveys throughout treatment, the timeline for survey collection was carefully crafted to decrease oversaturation (see Figure 2 for survey timeline). Specifically, participants will be asked to complete the PHQ-9 (which measures depression rates from minimal depression to severe depression) and the GAD-7 scale (a widely accepted anxiety scale that evaluates scores as either mild, moderate, or severe anxiety) on a daily basis [46,47]. Both the PHQ-9 and GAD-7 scales will be loaded on mindLAMP and become available to participants upon downloading.

Prior to each clinical visit, participants will briefly meet with a research assistant who will provide participants with a secure link (via REDCap) to weekly clinical surveys. This could be done via mindLAMP, but we will use a different platform for the purposes of this study. Those presession surveys include the Sheehan Disability Scale, which measures the effects of poor mental health across three domains: work and school, family, and social life [48]; the Primary Care Posttraumatic Stress Disorder-5, which assess for posttraumatic stress disorder [49]; the Behavior and Symptom Identification Scale-24, a symptom assessment scale [50]; a patient motivation scale, to asses participants commitment to change through treatment; the World Health Organization Five, a well-being assessment scale [51]; and the Working Alliance Inventory–Short Form, a scale to assess the alliance a patient feels toward the clinician that is known to be a predictor of treatment success (this scale will begin after session one) [52].

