Additional nonweekly scales include a participant satisfaction scale, which will be given after session four and at the end of treatment, and the System Usability Scale, which is offered during the termination process and is a well-accepted tool to assess satisfaction around use of mindLAMP and TECC [53]. The technology acceptance model, a well-known implementation science framework, will also be used to assess feasibility of technology-infused care [54]. Since the mindLAMP app is able to automatically capture data about when and how it is used, the study will offer a unique data set on longitudinal use patterns and engagement. A provider-specific satisfaction survey will be given to all referring providers at the end of the study to improve the referral process, assess the relevance of clinical data shared, and streamline continuation of care. Other metrics in this study include engagement with the app, as measured by number of log-ins each day, as well as time spent on each element of the app during each log-in. Basic demographics and measures of socioeconomic status will also be collected during the intake process.

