### Analysis

Analysis will include calculation of the effect size of TECC to reduce symptoms related to stress, anxiety, and depression. Analysis will also focus on assessing association between baseline factors, race, language, and education, as well as dynamic factors like working alliance and technology engagement patterns with changes in symptoms and use and adherence to the TECC protocol. We will assess relationships between these factors and clinical changes using generalized linear models and multiple regression analyses. Tests for dropout effects will be performed to see if outcome and covariate measures are associated with differences in engagement. If there are significant dropout effects, a logistic dropout probability model will be fit using the significant dropout outcomes and covariates measured at the start of the stage, and inverse probability weighting will be used with these model probabilities to account for dropout in each of the models. The age-matched control group will be used to compare changes related to clinical scores and calculate effect sizes using means and SDs.

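### The mechanism reading of engagement and alliance has no stated time order behind it, and raw log-ins include those made to complete the outcome scales

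*Protocol article*

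**What the plan says.** The protocol article fixes both an inference and a method.

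- **Inference (Introduction, hypotheses).** Out-of-session app engagement and in-session alliance "will be correlated with clinical improvements and suggest a mechanism of action for TECC".
- **Method (Results, Analysis).** The section plans to relate baseline factors and "dynamic factors like working alliance and technology engagement patterns with changes in symptoms and use and adherence to the TECC protocol". It then says: "We will assess relationships between these factors and clinical changes using generalized linear models and multiple regression analyses". No ordering of predictor before outcome is stated. The only time-ordered element is the dropout model, whose covariates come from the beginning of a stage.
- **Alliance (Study Measures).** The Working Alliance Inventory is among the surveys taken before each visit, and "this scale will begin after session one".
- **Engagement (Study Measures).** The metric is "engagement with the app, as measured by number of log-ins each day, as well as time spent on each element of the app".
- **Outcome scales (Interventions; Study Measures).** Participants "will be asked to begin completing the mood surveys (PHQ-9 and GAD-7) in mindLAMP on a daily basis", starting at least a week before the first visit. "Both the PHQ-9 and GAD-7 scales will be loaded on mindLAMP and become available to participants upon downloading".

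**The concern.** Alliance and app use change over the course of treatment, and so do symptoms. People who improve early tend to keep using an app and to rate their clinician well. If mean alliance or total app use over the eight sessions is related to total symptom change over the same period, a positive coefficient arises whether engagement drives improvement or improvement drives engagement. The article announces in advance that such a correlation would point to how TECC works. The Results section says that the findings will be used to keep or change the care model and to build training material. A signal produced by reverse causation could therefore shape what is disseminated.

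The engagement measure has a separate weakness. The outcome scales are completed daily inside the same app, so each log-in made to complete them adds to the log-in count. A high count may mean diligent survey completion and not practice of skills.

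**Working it through.** The article attaches no figure to this analysis, so there is nothing to reproduce. The numbers below are illustrations under stated assumptions.

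**Inputs from the article.** 50 participants; 8 sessions; alliance measured before each visit from after session one, so 8 − 1 = 7 readings; PHQ-9 and GAD-7 daily in the app; engagement as log-ins per day plus time on each app element. **Assumed.** Two-sided 5% level, 80% power, and the feedback strengths below.

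**1. Direction.** Simulation, 4,000 runs, 50 people, 8 sessions. Each session adds to improvement a step of 0.5 × (personal slope)/8 + 0.87 × (noise)/√8, with standard normal slope and noise. Alliance is a person component plus an occasion component (variance 0.5 each) plus b × improvement up to the previous session. Alliance has no effect on improvement, so every significant result is false as evidence of mechanism.

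| Feedback b | Mean alliance vs total change (same window) | Second-session alliance vs change from then to session 8 |
|---|---|---|
| 0 | 4.7% | 4.7% |
| 0.3 | 28.8% | 4.9% |
| 0.5 | 60.1% | 5.1% |
| 1.0 | 98.2% | 5.0% |

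The same-window regression has the right error rate only when there is no feedback. Ordering the measures restores it here. One caution applies: personal slopes are weak in this set-up. If people follow strongly persistent trajectories, early alliance carries information about the later slope, and ordering alone is not enough. The later-change model therefore also needs baseline and the score at the start of the later period.

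**2. Log-ins.** If the surveys take one log-in a day (assumed) and skill practice takes k log-ins a day, the survey share is 1/(1 + k). For k = 0.25 this is 1/1.25 = 80%; for k = 0.5, 67%; for k = 1, 50%.

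**3. One row per participant.** The smallest correlation detectable with 80% power is tanh((1.96 + 0.84)/√(50 − 3)) = tanh(0.409) ≈ 0.39. Using one row per participant makes the rows independent, but does not settle direction.

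**4. If repeated rows were used.** With 7 readings and the same intraclass correlation ρ in predictor and outcome, the variance inflation from treating rows as independent is about 1 + 6ρ². At ρ = 0.4 this is 1.96, and the error rate is 2(1 − Φ(1.96/√1.96)) ≈ 16%. At ρ = 0.7 it is 3.94, and the error rate is 2(1 − Φ(1.96/√3.94)) ≈ 32%. This applies only if rows are stacked without allowance for clustering, which the article does not say.

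**The case against.** The strongest reply is that the article leaves these details open and that a fuller plan may settle them. Much of that stands, and it limits the point in four ways.

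- A reader might infer that repeated readings will be stacked as if independent, making the standard errors wrong. The article does not say so. It speaks of changes in symptoms, and one change score per person is a natural reading, under which independence holds.
- A reader might infer that concurrent readings are to be paired. The text does not say which reading goes with which change. What can be said is that nothing requires the predictor to come first.
- A reader might conclude that log-ins for surveys create a spurious correlation with improvement. That is not shown: completing more questionnaires does not in itself lower the score. Log-ins are also only one of two stated metrics. Time on each app element is recorded, so survey use can be separated from skill use, though the text does not say that it will be.
- The claim is cautious: the hypothesis uses the language of correlation and suggestion, the Analysis section speaks of association, and the Abstract lists engagement and alliance among secondary outcomes.

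The reply does not remove the core. The article itself states both what the correlation will be taken to indicate and which models will produce it. It specifies time order for dropout but not for the question that depends on it most.

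**Conclusion.** The point holds in limited form. The regressions named in the Analysis section, without a stated time order, cannot support the mechanism reading in the Introduction. Under assumed feedback of 0.3 to 1.0, a same-window regression is significant in about 29% to 98% of runs with no true effect, against about 5% when time-ordered. These rates depend on the simulated feedback and on weak personal slopes; they are not estimates for this trial. Raw log-ins partly measure outcome completion, perhaps 50% to 80% of the count under the assumed log-in pattern. That is a problem of what the variable means, not a demonstrated bias. The documents do not support a claim that the standard errors will be wrong. The point concerns a secondary inference and leaves the main symptom outcomes untouched, but it should be corrected because better use of data already being collected would resolve it.

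**What to change.** 1. Base any mechanism statement on a time-ordered analysis: alliance and engagement from the early sessions predicting later change in PHQ-9 and GAD-7, one row per participant, adjusted for baseline and for the score at the start of the later period. State the split between early and late sessions in advance.
2. If repeated rows are used, fit a mixed model or generalized estimating equations with clustering by participant. Do not rest the inference on a person-mean-centred coefficient in a model that also contains the lagged outcome. The person mean includes alliance readings taken after the outcome. In a null simulation with 50 people and 7 lagged rows, that coefficient was falsely significant in 19%, 43% and 98% of runs at feedback 0.3, 0.5 and 1.0.
3. Define engagement from time on skill-activity elements, which the app already records, and exclude log-ins made only to complete PHQ-9 or GAD-7.
4. In the Introduction, describe same-window correlations as associations only.

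**Cost.** No new measurements. The outcome window is shorter, precision is somewhat lower (already limited to correlations of about 0.39 with 50 participants), and there is a little more analysis work.

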### Session Two: Identifying Thought Patterns

The second skill will focus specifically on understanding and identifying thought patterns. CBT will be introduced using a core CBT principle, ensuring information is presented in a structured and educational method, which allows for in-the-moment focus and client participation [30]. Again, mindLAMP will assist in this process by providing clients with out-of-session education and activities. mindLAMP activities will include documenting, describing, and labeling different types of thinking patterns.

Studies have shown that CBT smartphone apps have therapeutic potential [31]; however, like many apps, high user engagement and sufficient long-term outcomes seem to be the top barriers for effective CBT app outcomes [32]. User engagement will be closely monitored through review of out-of-session activities, incorporating participant feedback when applicable, and monitoring participants overall engagement to care. Figure 7 provides an example of a mindLAMP activity that can be used for this skill.

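### The dropout screen tests measures against engagement rather than dropout, so variables for the dropout weights are chosen on a different event from the one modelled

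*Protocol article*

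**What the plan says.** The Analysis section sets out a three-step rule.

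1. Screen: "Tests for dropout effects will be performed to see if outcome and covariate measures are associated with differences in engagement".
2. If the screen is significant, "a logistic dropout probability model will be fit using the significant dropout outcomes and covariates measured at the start of the stage".
3. Then "inverse probability weighting will be used with these model probabilities to account for dropout in each of the models".

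The only operational definition of engagement is in Study Measures: "engagement with the app, as measured by number of log-ins each day, as well as time spent on each element of the app". The Introduction hypothesises that "rates of app engagement out of sessions, as well as therapeutic alliance measured during sessions, will be correlated with clinical improvements". The abstract lists engagement among the secondary outcomes. The Analysis section itself also uses technology engagement as an explanatory factor for symptom change.

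Dropout is treated as something else. Further Study Details keeps participants who leave in the intent-to-treat analysis. The Discussion names high app engagement and low dropout as two separate aims. A looser use of the word appears once, under Session Two: "monitoring participants overall engagement to care". That broader sense is neither defined nor given a measure.

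**The concern.** A screen for informative dropout should ask which measures differ between those who leave and those who stay. Here the screen asks which measures go with engagement, and its answer becomes the predictor list of a dropout model. Two errors can follow.

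- **False label.** A measure related to app use but not to leaving is reported as a dropout effect and starts the weighting. If the engagement hypothesis is true, this becomes more likely for symptom scores.
- **Missed driver.** A measure that makes people leave but has little to do with app use is not selected, so the weights do not correct for it.

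The second matters more. Weighting is the plan's stated protection for the symptom-change results against informative dropout, and it works only if the variables that drive dropout are in the model. The point is separate from whether weighting should depend on a significance test at all: at any threshold, the tested variable is the wrong one.

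**Working it through.** The documents give no alpha, dropout rate, correlation or effect size for this step, so there is no stated figure to reproduce. The only input taken from the protocol is n = 50 (Methods, Study). Everything else is an assumption: two-sided alpha 0.05; dropout of 15%, 25% or 40%; correlations and log-odds as shown.

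**A. Measure related to engagement, unrelated to dropout.** The chance that the screen as written is significant is, by Fisher's z, approximately Φ(atanh(r) × √(n − 3) − 1.96), with √47 = 6.856.

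| r | atanh(r) × 6.856 | minus 1.96 | flagged by engagement screen |
|---|---|---|---|
| 0.2 | 1.390 | −0.570 | 28% |
| 0.3 | 2.122 | 0.162 | 56% |
| 0.4 | 2.904 | 0.944 | 83% |
| 0.5 | 3.766 | 1.806 | 97% |

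Simulation (up to 4,000 runs per scenario) agrees within about 2 percentage points. A t-test of dropouts against completers flags the same measure about 5% of the time, whatever r is.

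**B. Measure drives dropout, unrelated to engagement.** The engagement screen flags it about 5% of the time, which is simply its type I error rate. A direct test against dropout does this:

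| log-odds of dropout per SD | 25% dropout | range over 15% to 40% dropout |
|---|---|---|
| 0.7 | 50% | 37% to 61% |
| 1.0 | 77% | 61% to 87% |
| 1.5 | 96% | 87% to 99% |

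**C. Measure drives dropout and correlates with engagement at −0.4.** The engagement screen flags it about 83% of the time, so it is not missed.

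**Between B and C.** App use may be totalled over the course, so that leaving early lowers it mechanically. With 10 dropouts among 50 who differ by 0.8, 1.0 or 1.2 SD on the measure, the engagement screen finds it about 16%, 23% or 28% of the time with total use on the log scale, and less often on the raw scale. A direct test finds it 60%, 79% or 91% of the time.

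**Bias if a driver is left out (25% dropout, large sample).** Bias of the completers' mean, in outcome SDs, absolute value:

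| log-odds per SD | measure–outcome correlation 0.3 | correlation 0.5 |
|---|---|---|
| 0.7 | 0.05 | 0.08 |
| 1.0 | 0.06 | 0.11 |
| 1.5 | 0.08 | 0.14 |

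With weights that include the driver, the remaining bias is below 0.001 SD in every cell.

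**The case against.** The strongest reply concerns the word itself. The sentence says engagement without qualification, whereas the authors usually write app or technology engagement when they mean use of the app. The sentence stands among repeated references to dropout, and Session Two speaks of engagement in care. Read that way, the screen compares people who stayed with people who did not, and one word is loose. This reading is possible. But engagement in care is never defined or measured, and Further Study Details asks people who miss four consecutive sessions to restart, so poor attendance is not the same as leaving. This reading narrows the point but still calls for the same correction.

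A reader might infer that the screen must be significant whenever the engagement hypothesis is true. The documents do not support that. The hypothesis concerns improvement, while the dropout model takes levels at the start of a stage, and a correlation with change does not imply one with level, least of all at the first stage. Scores at the start of stages 2 and 3 do carry earlier improvement, so the link is plausible there, but it remains a question of power: 28% at r = 0.2.

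A reader might also infer that drivers of dropout are missed in general. They are missed when weakly related or unrelated to engagement. The 5% in scenario B follows from assuming no relation, and scenario C shows the opposite case.

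Two further points stand. The second step still regresses actual dropout on the selected measures, so a wrongly selected one gets a coefficient near zero and mainly adds noise. And the bias is modest against sampling error: at 25% dropout, 50 × 0.75 = 37.5 completers give a standard error of a mean of 1/√37.5 = 0.16 SD.

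How dropout is coded in detail may fairly be left to a fuller document. The mismatch between the screened variable and the modelled event is in what the article states, so it cannot be deferred in the same way.

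**Conclusion.** The point holds in limited form. Followed as written, the rule selects predictors of dropout by their association with engagement, which the protocol measures as app use and treats elsewhere as an outcome and a possible mechanism. False selection is a matter of labelling and noise. Omission of a driver weakly related to engagement is the substantive risk, with a residual bias of about 0.05 to 0.14 SD for log-odds of 0.7 to 1.5 per SD, measure–outcome correlations of 0.3 to 0.5 and 25% dropout. All these inputs are assumed. The documents do not show that any such driver exists, nor how closely engagement will track dropout. The correction should be made because the step decides both whether the results are weighted and by what, and because it costs almost nothing.

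**What to change.** In the Analysis section, change the screen so that outcome and covariate measures at the start of each stage are tested against dropout itself. Dropout should be defined as a yes/no event per stage, for example not starting the next stage or having no final PHQ-9 or GAD-7 score, with a statement of how participants who restart are counted. Alternatively, prespecify a small set of covariates for the dropout model and drop the screen. Start-of-stage app engagement may be a candidate predictor in that model but should not be the variable the screen tests against. Keep the association between engagement and outcome as the separate mechanism analysis announced in the Introduction.

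The cost is a sentence or two of wording. No new type of data is needed, since session attendance and score availability arise from the planned sessions and surveys. The limitation is size: 15% to 40% dropout among 50 participants is about 8 to 20 events, so the dropout model can hold only a few predictors. That limit applies to the present rule as well, and it favours a short prespecified list.
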